## **5. TREATMENT OF SUBJECTS**

### **5.1 Investigational product/treatment**

Control condition: Participants in the waiting list condition will be seen once by a study therapist and informed about the course of the study. After three months patients will be offered the opportunity of following a standard treatment for their PD. This period is shorter than the regular waiting time for treatment of PD, which ranges 6 to 12 months.

Experimental condition: The Dutch version of the standard EMDR protocol (de Jongh & ten Broeke, 2019) will be used. The protocol will focus on the most distressing target memory. A total of 10 biweekly sessions of EMDR will be applied with a duration of 90 minutes per session. EMDR therapists are psychologists who have followed at least the basic EMDR training certified according to the guidelines of EMDR Europe. Group supervisions will be provided monthly by consultants in the treatment of EMDR. Additional supervision by telephone or e-mail is available on request. The treatment sessions will be videotaped; 10% will be randomly selected and rated by trained and blinded raters for therapist competence and treatment protocol adherence.

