## 1. INTRODUCTION AND RATIONALE

### Statement of the problem

Prevalence rates for childhood trauma among patients with personality disorders (PD) are very high. Verbal -, physical - and sexual abuse during childhood have been reported in, respectively, 72%, 46% and 26% of patients with borderline personality disorder (BPD, Zanarini, Gunderson, Marino, Schwartz, & Frankenburg, 1989). A total of ninety-seven percent of BPD patients were found to have experienced at least one type of childhood trauma, i.e., emotional -, physical – or sexual abuse, or emotional – and physical neglect at our department. Among different types of PD high prevalence rates were reported for abuse (73%) and neglect (82%, Battle et al., 2004). Estimates of the prevalence of PTSD in patients with BPD range 34% to 56% (Slotema, Blom, Niemantsverdriet, Deen & Sommer, 2018; Zanarini et al., 1998). For patients with other PD than BPD prevalence rates for PTSD vary between 20 and 47% (Goldstein et al., 2017; Zanarini et al., 1998; Yen et al., 2002). Psychotherapy is the treatment of first choice for patients with PD. However, training of therapists and the long duration of treatment are accompanied with high costs. Furthermore, symptoms are found to remain unchanged or exacerbate during psychotherapy for PD in 34 up to 57% (Giesen-Bloo et al., 2006; Svartberg, Stiles, & Seltzer, 2004; own data from clinical practice). Given these concerns, the high prevalence of trauma and associated consequences, the question arises whether treatment of patients with PD can be improved if interventions will be used that focus on trauma memories. There is mounting evidence suggesting that EMDR therapy is not only effective in the treatment of PD with and without PTSD but also efficient, and thus cost-effective. The need to improve the treatment of PD with interventions that focus on trauma is clear. The next step is to conduct a sufficiently powered RCT for patients with all types of PD to explore the efficacy and cost-effectiveness of EMDR compared to waiting list to confirm these preliminary results and to determine the effects in terms of loss of diagnoses and cost-saving one year following treatment.

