## 2. OBJECTIVES

### *Primary Objectives:*

- 1) How effective is EMDR therapy compared to waiting list on symptoms of PD?
- 2) How cost-effective is EMDR therapy versus a wait-list control condition?

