## 8.3 Study procedures

1. Patients will be recruited in two ways; 1. by means of posters hanging in the waiting room; patients can announce themselves to their treating therapist/physician or contact the researchers directly 2. Patients with a PD will be informed by the therapist/physician about the study. The therapist/physician informs the researchers, who will send information to the patient by mail and call the patients to invite them for an appointment. Interested patients will receive further information about the study during an appointment with one of the researchers. Furthermore, the researcher will check eligibility for inclusion. At the end of the appointment patients will be given informed consent forms. The patients are allowed to take the time they need to make a decision about participation. Patients who decide to participate will be asked to sign informed consent.
2. Diagnostic instruments before inclusion: a. Any PD diagnosis will be confirmed using the SCID-5-PD
3. Informed consent: During an intake interview with the researchers, patients are informed about the study verbally and formally. If the patient had enough time to consider whether he/she wants to participate into this study, the patient is asked to give written, informed consent.
4. Randomization: After patients are included and have given informed consent, patients are randomized into one of the two conditions.
5. Questionnaires will be administered at baseline (before randomization), after weeks (post EMDR) and three, six and twelve months after onset of the study.
6. Interview: all participants in the EMDR group will be requested to participate in a qualitative interview about their experiences with EMDR therapy.
7. Patients in the experimental group are treated with ten biweekly, ninety minute, EMDR sessions. These patients are compared with a waiting list condition. After three months of follow-up patients can decide whether they want to have standard treatment for PD.

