### 10.2 Secondary study parameter(s)

Mixed models with intention-to-treat will be used to compare EMDR and waiting list qua (1) the decline of diagnoses of PD, (2) the severity of psychotrauma and PTSD symptoms and (3) the severity of difficulties in emotion regulation and interpersonal functioning. The economic evaluation will be undertaken according to the Dutch guidelines for costs effectiveness studies taken a societal perspective (Hakkaart et al., 2016). The severity (i.e., number of symptoms) of PD, aided by the ADP-IV, will be used for effectiveness. The TiC-P is used to collect data on utilization of medical services and productivity loss. Utility scores are estimated using the EQ-5D-5L and MHQoL will measure the effects. A cost-utility analysis and a cost-effectiveness analysis (CEA) are conducted. The cost-utility is calculated as the incremental costs and utilities, which yields a cost per QALY estimate. The cost-effectiveness is expressed in the incremental costs and scores on the SCID-5-PD.

Multilevel modeling is used to model cost-effectiveness. For assessing the uncertainty, cost effectiveness acceptability curves and cost effectiveness planes will be created after bootstrapping. The acceptability curve illustrates the probability that the cost-effectiveness ratio will be accepted for different thresholds. In a cost-effectiveness plane, both incremental costs and incremental effects are plotted to account for combinations.

Sensitivity analyses will be performed after the analysis if necessary.

Qualitative data on patients' experiences with EMDR therapy will be summarised by the researchers and provided to participants for respondent validation. The researchers will

thoroughly read all transcripts, highlight all potentially relevant excerpts and sort them based on the research questions. These sorted data will then be independently coded by the researchers; excerpts will be grouped based on their similarities. Then, these groupings will be identified/themed. Consequently, the researchers will confer and attempt to reach consensus on all groupings and themes, resulting in a preliminary codebook. The codebook and two information rich transcripts as examples will be presented to the study group. Themes will be reviewed, focussing on understanding the data and confirming that the data still correspond to the assigned themes.

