### 11.4 Benefits and risks assessment, group relatedness

Patients with PD suffer from low self-esteem, have severe impairments in the regulation of emotions and interpersonal functioning and their quality of life is low. In a recent study, EMDR reduced BPD symptoms (De Jongh et al. 2020). In another study, psychological symptoms, psychological functioning, and personality functioning were positively affected by 5 EMDR sessions in all PDs (Hafkemeijer et al., submitted for publication). Thus, it is expected that patients who receive EMDR, will experience a reduction in PD symptoms and an improvement in psychological and personality functioning. In addition, EMDR is safe and not associated with an increase of self-injurious behaviour, suicidal gestures, suicides or hospital admissions. is applied in addition to treatment as usual for PD with regular meetings. In case emotions or traumatic intrusions increase in the two or three days after a session of EMDR, patients have the opportunity to discuss their symptoms with the EMDR- and PD-therapists. Also, no risks are expected due to the data collection.

The study requires participants in the control group to not receive treatment for three months. If necessary or if the participant no longer wants to participate, he or she is free to terminate participation.

With participation into this study, patients contribute to knowledge about treatment and can therefore contribute to the quality of treatment.

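### The 12-month economic comparison is labelled EMDR versus waiting list, but controls are offered standard PD treatment after 3 months, and the sections disagree on access by arm

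*Protocol*

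**What the plan says.** Protocol section 2 lists as a primary objective: "How cost-effective is EMDR therapy versus a wait-list control condition". Section 1 (Statement of the problem) says the trial is also meant "to determine the effects in terms of loss of diagnoses and cost-saving one year following treatment". Section 3 schedules assessments at baseline, 5 weeks, and 3, 6 and 12 months.

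The control condition is described in section 5.1: "After three months patients will be offered the opportunity of following a standard treatment for their PD". The next sentence adds: "This period is shorter than the regular waiting time for treatment of PD, which ranges 6 to 12 months". Section 11.4 confirms the length of the untreated period: "The study requires participants in the control group to not receive treatment for three months".

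The economic evaluation is in section 10.2. It takes a societal perspective and derives a cost per QALY and a cost per effect. On resource use it says: "The TiC-P is used to collect data on utilization of medical services and productivity loss". It states no time horizon, does not say what the comparator is after month 3, and allows sensitivity analyses only as needed after the main analysis.

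On access to standard treatment, section 8.3 item 7 describes both arms and then says: "After three months of follow-up patients can decide whether they want to have standard treatment for PD". Section 11.4, in a sentence whose subject is missing, says that something "is applied in addition to treatment as usual for PD with regular meetings", and it goes on to mention PD therapists alongside EMDR therapists.

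**The concern.** The objective names a waiting list as comparator, but under the plan that comparator ends at month 3. From then on controls may use standard PD treatment, which section 1 itself calls long and expensive. Its costs enter through the TiC-P and any benefit enters the utilities and PD outcomes. A ratio over 12 months is thus built mostly from a period in which controls need not be waiting.

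What is at stake is the conclusion. A 12-month result reported under the wording of objective 2 would be taken to show what EMDR saves against leaving patients on the list. In clinics with the wait that the protocol describes, patients would reach standard treatment later than trial controls can.

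There is a second problem. The incremental cost depends on what the EMDR arm may receive and when, and the protocol does not give one answer.

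**Working it through.** The plan gives no economic figure to reproduce, and its sample size does not enter this point. The check is arithmetic on time, followed by a comparison of the access passages.

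**Inputs**
- Horizon H = 12 months. This is inferred from sections 1 and 3, since 10.2 states none.
- Wait in the trial: 3 months (5.1, 11.4).
- Regular wait: 6 to 12 months (5.1).
- Post-baseline assessments: 5 weeks, 3, 6 and 12 months (3).

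**Share of the horizon spent waiting** = wait / H
- Trial: 3/12 = 25%.
- Regular practice: 6/12 = 50% to 12/12 = 100%.

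**Months of possible access to standard treatment** = H − wait
- Trial: 12 − 3 = 9.
- Regular practice: 12 − 6 = 6, down to 12 − 12 = 0.
- Extra access in the trial: 9 − 6 = 3, up to 9 − 0 = 9 months.

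Two of the four post-baseline assessments (6 and 12 months) fall after access opens.

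The 3 to 9 months are an upper bound, for two reasons. Access is not treatment received, because the offer is optional and no uptake is given. The two waits may also start on different dates. The trial's wait starts with the study, while the protocol does not say when the regular wait starts. If a participant had already waited, say, 3 months before enrolment (an assumption), the extra access falls to (6 − 3) − 3 = 0, up to (12 − 3) − 3 = 6 months.

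**Scale on the QALY side (assumption only).** Suppose standard treatment raised utility by 0.02 to 0.10 from the day of access, with full uptake. Extra QALYs in controls = gain × extra months / 12:
- Against a 6-month wait: 0.02 × 3/12 = 0.005 to 0.10 × 3/12 = 0.025.
- Against a 12-month wait: 0.02 × 9/12 = 0.015 to 0.10 × 9/12 = 0.075.

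The protocol gives no utility gain, uptake or unit cost, so the effect on the ratio itself cannot be computed.

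**Access by arm, side by side**

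| Section | What it says on standard PD treatment | What it implies for the EMDR arm |
|---|---|---|
| 5.1 | Offered at 3 months, under the control condition only | Not stated |
| 8.3 item 7 | Patients may choose it at 3 months, arm not named | Possibly the same access from month 3 |
| 11.4 | Something is added to usual PD treatment; PD therapists are available | Possibly usual treatment from the start |
| 5.2 | Co-intervention not applicable | None, if taken literally |

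Appendix A question 7 also asks EMDR participants about their main treatment, which presupposes one. Each reading gives a different incremental cost. Under none of them do months 3 to 12 compare EMDR with waiting alone.

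**The case against.** The strongest reply is that nothing is hidden. Section 5.1 defines the waiting-list condition, including the 3-month offer, and openly says that it is shorter than usual. The 12-month contrast remains a valid randomised comparison of two pathways. Section 1 also hopes that EMDR will shorten later PD treatment, so counting later treatment costs is part of the intended effect in a societal evaluation. Horizon, base case and cost breakdown are commonly left to an analysis plan, which is not shown. Much of this stands: the point concerns naming and interpretation, not an invalid estimate. It does not dispose of the point, because the objective, the comparator and what each arm is offered are fixed in this protocol, and an analysis plan cannot settle the last of these.

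A reader might infer more than the document supports:

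- *That the trial gives controls 3 to 9 extra months of treatment.* It offers treatment. Uptake and the start of the regular wait are not stated.
- *That the design makes EMDR look cost-saving.* Earlier standard treatment could raise control costs and could also improve control outcomes, and these pull in different directions. If 8.3 means that both arms may start at month 3, access from then on is symmetric and a cost artefact from a one-sided offer largely disappears.
- *That the first 3 months should be the base case.* That window carries the full cost of ten sessions delivered in 5 weeks, caps attainable QALYs at 3/12 = 0.25 per person, and cannot answer the one-year question in section 1.

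**Conclusion.** The point holds as a mismatch between objective, comparator and horizon. Over 12 months the trial compares EMDR with a 3-month wait followed by optional standard PD treatment. That result should not be presented as cost-effectiveness against waiting, or as a saving against the regular 6 to 12 months.

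Controls are on the list for 25% of the horizon, against 50% to 100% at the regular wait, and their extra access is at most 3 to 9 months. These figures assume a 12-month economic horizon and, for the regular wait, a count from study onset. The size and direction of the effect on the ratio cannot be derived from the document.

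Separately, sections 5.1, 8.3 and 11.4 do not agree on which arm has access to standard treatment and from when, so the incremental cost is not clearly defined. The 3-month offer itself is not criticised here, and no sample-size or power figure is affected.

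**What to change.** 1. In objective 2 and section 10.2, keep the 12-month analysis but name its comparator as a 3-month wait followed by an offer of standard PD treatment, and limit the conclusion to that comparison.
2. Prespecify a supplementary comparison from baseline to 3 months, not as the base case. It is the only period with a true EMDR versus waiting-list contrast, provided item 4 confirms that the EMDR arm has no other PD treatment in that time. State that it carries all of the EMDR cost and little of any later benefit.
3. Report TiC-P costs of standard PD treatment as a separate line for each arm.
4. Reconcile sections 5.1, 8.3 item 7 and 11.4 (and the entry in 5.2) on which arms have access to standard PD treatment and from when. Which rule applies is for the sponsor to decide.

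The cost is wording in these sections and slightly more analysis work. Section 8.3 already schedules questionnaires at 3 months, so no new visit is needed. The price to the sponsor is a narrower 12-month claim.

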### **5.2 Use of co-intervention**

NA

### **5.3 Escape medication**

NA

## 6. INVESTIGATIONAL PRODUCT

*<This chapter is applicable for research with any product; medicinal product, food product, medical device or other >*

NA

6.1 Name and description of investigational product(s)

6.2 Summary of findings from non-clinical studies

*<One may refer to the Investigator's Brochure (IB), Investigational Medicinal Product Dossier (IMPD), Summary of Product Characteristics (SPC) or a similar document (if applicable), by mentioning the relevant pages in that document. Be sure that the information is up to date and references to peer reviewed papers in (biomedical/scientific) journals should be given where appropriate.>*

6.3 Summary of findings from clinical studies

*<See explanatory text of chapter 6.2, including remark>*

6.4 Summary of known and potential risks and benefits

*<See explanatory text of chapter 6.2, including remark>*

6.5 Description and justification of route of administration and dosage

6.6 Dosages, dosage modifications and method of administration

6.7 Preparation and labelling of Investigational Medicinal Product

6.8 Drug accountability

*<Please describe the procedures for the shipment, receipt, disposition, return and destruction of the investigational medicinal products.>*

**7. NON-INVESTIGATIONAL PRODUCT**

NA

## 8. METHODS

### 8.1 Study parameters/endpoints

#### 8.1.1 Main study parameter/endpoint

- Assessment van DSM Persoonlijkheidsstoornissen-IV (ADP-IV) vragenlijst ( $\alpha = .76-.77$ ; Doering et al., 2007; Schotte et al., 1998; 2004)
- Clinician-Administered PTSD Scale for DSM-5 (CAPS-5;  $\alpha = .90$ ; Boeschoten et al., 2014a; 2018)

#### 8.1.2 Secondary study parameters/endpoints (if applicable)

- Structured Clinical Interview for DSM 5 Personality Disorders (SCID-5-PD;  $\kappa = .6-.83$ ; Maffei et al., 1997)
- Jeugd Trauma Vragenlijst (JTV, Bernstein et al., 1997)
- Life Events Checklist for the DSM-5 (LEC-5, Gray et al., 2004)
- Level of Personality Functioning Scale - Brief Form 2.0 (LPFS-BF 2.0, Hutsebaut et al., 2015)
- PTSD Check List (PCL;  $\alpha = .93$ ; Boeschoten et al., 2014b; Van Praag, 2020)
- Difficulties in Emotion Regulation Scale (DERS;  $\alpha = .81$ ; Gratz & Roemer, 2004; Neuman et al., 2010)
- Brief State Paranoia Checklist (BSPC, Schlier, Moritz, & Lincoln, 2016)
- Outcome Questionnaire-45 (OQ-45;  $\alpha = .93$ ; De Jong et al., 2007; 2008)
- Euro-Quality of Life 5 dimension 5 level version (EQ-5D-5L;  $\alpha$  not clear; EuroQol Group, 1990)
- Treatment inventory Cost In Psychiatric Patients (TiC-P;  $\kappa = .49-.84$ ; Bouwmans et al., 2013)
- Mental Health Quality of Life questionnaire (MHQoL, Cronbach's  $\alpha = .86$ , Ware, Kosinski, Dewey, & Gandek, 2001)
- A self-designed interview about experiences with EMDR therapy (see: appendix A).
- Number of dropouts

#### 8.1.3 Other study parameters (if applicable)

- Broad demographic data will be collected to explore which patient will (not) benefit from EMDR.

## 8.2 Randomisation, blinding and treatment allocation

The study is single-blind. Considering the nature of the study, double-blinding is impossible; study participants know that they are receiving EMDR. However, researchers for data collection can be held ignorant of the condition the participant is in. Random allocation to one of the treatment arms will be performed with the use of the website: [www.randomization.com](http://www.randomization.com). A password protected randomization list that is accessible by the coordinating and principle researchers will be kept on the server. The researchers will establish contact between participant and EMDR therapist.

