### 11.2 Recruitment and consent

Recruitment will be at GGZ Delfland and multiple institutions of Parnassia Psychiatric Institute. Patients will be recruited in two ways. 1. By means of posters hanging in the waiting room; patients can announce themselves to their treating therapist/physician or the investigator. 2. Patients with the relevant diagnosis will be informed by their therapist/physician about the research. If the patient is interested, the therapist/physician informs the researchers, who will call the patients to invite them for an appointment. At this appointment, the researchers will provide the patients with further information and check eligibility for inclusion. If patients meet the inclusion criteria, they will receive the informed consent form, which they are allowed to sign right away, or whenever they feel ready. The written, informed consent of the patient will be collected by the researcher.

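### The protocol does not separate access to the randomization list from enrolment or outcome assessment, so neither allocation concealment nor assessor blinding is secured

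*Protocol*

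**What the plan says.** Section 8.2 contains the whole allocation mechanism:

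- **Source of the sequence:** "Random allocation to one of the treatment arms will be performed with the use of the website".
- **Custody:** "A password protected randomization list that is accessible by the coordinating and principle researchers will be kept on the server".
- **Acting on the allocation:** "The researchers will establish contact between participant and EMDR therapist".
- **Blinding:** the trial is called single-blind. Participants know their arm, but "researchers for data collection can be held ignorant of the condition the participant is in".

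Enrolment is described in sections 8.3 and 11.2. On information before consent: "During an intake interview with the researchers, patients are informed about the study verbally and formally". On eligibility: "Furthermore, the researcher will check eligibility for inclusion". On consent: "The written, informed consent of the patient will be collected by the researcher". One of the three inclusion criteria in section 4.2 is distress from traumatic experiences, with no instrument or cut-off attached.

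On sequence, section 8.3 places randomization after inclusion and consent, and baseline questionnaires before randomization. The same section adds a contact that occurs in one arm only: "all participants in the EMDR group will be requested to participate in a qualitative interview about their experiences with EMDR therapy".

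**The concern.** Allocation concealment requires that whoever decides whether and when a patient enters cannot know the next assignment. Here a readable list exists inside the research team, one entry criterion is discretionary, and patients may take as long as they need to decide, so the order of entry is flexible. Under those conditions a patient can be advanced, delayed or declined in the light of the next assignment. The resulting imbalance would affect every outcome, including the self-reported ADP-IV. The mixed model in section 10.1 carries baseline as one of its five time levels and can deal partly with measured baseline differences, but not with unmeasured ones.

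Assessor blinding is a separate matter with a narrower reach. The ADP-IV is a questionnaire completed by participants who know their arm, so blinding the assessor protects it little. The outcomes that blinding can protect are the interviewer-rated ones:

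- the CAPS-5, listed as a main endpoint in section 8.1.1;
- the SCID-5-PD, in whose scores section 10.2 expresses cost-effectiveness. Cost-effectiveness is a primary objective in section 2.

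**Working it through.** The point is procedural and has no figure to reproduce. The check is to set the sections side by side and ask, for each step, who performs it and whether the protocol keeps that person apart from the list.

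| Step | Who, according to the protocol | Separated from list access? |
|---|---|---|
| Holding the list (8.2) | Coordinating and principal researchers, by password | They are the list holders |
| Inviting and informing (8.3, 11.2) | The researchers | Not stated |
| Checking eligibility (8.3, 11.2) | The researcher | Not stated |
| Collecting consent (11.2) | The researcher | Not stated |
| Linking participant to EMDR therapist (8.2) | The researchers | Not stated |
| Collecting outcome data (8.2) | Researchers for data collection | Ignorance of arm said to be possible; no procedure |
| EMDR experience interview (8.3, Appendix A) | The researcher; timing not given | Not stated |

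1. **Can anyone on the team know the next assignment?** A stored list opened by password is most naturally read as a sequence drawn up in advance. On that reading, anyone with the password can see the next entry. The protocol describes no independent holder and no release of one assignment at a time.

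2. **Can that person influence entry?** No section bars list holders from recruiting, screening or taking consent, and the enrolment steps name researchers generically. Following the plan as written therefore permits foreknowledge at the point of enrolment.

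3. **Does the order of events prevent this?** No. Randomizing after consent and baseline stops the assignment from being made early. It does not stop the next entry from being read early.

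4. **Are outcome raters kept blind?** The only text is the possibility quoted from section 8.2. Two stated activities work against it. Whoever links a participant to the EMDR therapist learns the arm, and whoever conducts the EMDR interview learns it too. Neither activity is closed to raters. By contrast, section 5.1 commits to blinded raters for the sample of session videos, and the outcome interviews have no equivalent commitment.

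5. **How large is the effect?** The document gives nothing from which the frequency of selective enrolment, or its effect on an outcome, could be computed. No number is offered.

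**The case against.** The strongest reply is that the protocol does recognize different roles. List access is restricted by password to the coordinating and principal researchers, section 8.2 speaks separately of researchers who collect data, and section 12.1 reserves the participant code key to the main researchers. The people who screen and rate may well be others. This stands as far as it goes: a reader might infer that the list holders are the people who enrol, and the document does not say so. But section 12.1 concerns only the code key, and no section turns the difference in titles into a rule. That rule is the safeguard.

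Three other stronger readings are also unsupported:

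- **That all 159 allocations are foreseeable.** Section 8.2 does not say when the list is generated or how long it is. Generation in advance is the likely reading, but it remains an inference.
- **That single-blinding fails.** Lack of a described safeguard means that blinding is not assured. It does not show that blinding is broken.
- **That the EMDR interview unblinds the raters.** Neither its timing nor a separate interviewer is specified. The questions in Appendix A look back on treatment, which fits a late interview. It is a route to unblinding that has been left open, not one shown to be used.

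It can also be said that waiting-list participants see a study therapist once (section 5.1), so a therapist appointment need not by itself reveal the arm. That is fair, but section 8.2 refers to contact with an EMDR therapist, and the person arranging it would ordinarily know why.

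Finally, this is not detail that belongs in an analysis plan. Who holds the list and who rates outcomes is trial conduct, which section 8.2 sets out to define.

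**Conclusion.** The concern holds as a missing separation of roles around a list that the protocol itself makes readable within the research team. Allocation concealment is not secured, and assessor blinding is not secured for CAPS-5 and SCID-5-PD. The conclusion rests on the list being readable before enrolment decisions are made, which is the natural but unstated reading of section 8.2. It does not require that list holders actually enrol or rate patients, only that nothing prevents it.

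The size of any bias cannot be quantified from the document. The case for correcting this before patients are allocated is that selective enrolment cannot be undone afterwards and cannot be reliably repaired in the analysis.

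**What to change.** Amend section 8.2 to state that:

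1. Nobody who recruits, screens, takes consent or rates outcomes can read the list. It is held by a team member with none of those roles, or in the data management system of section 12.2 if that system supports randomization, which the protocol does not say.
2. Each allocation is released singly, and only after eligibility, consent and baseline are recorded. The order already exists in section 8.3. The recorded check and the independent release are new.
3. A team member who does not rate outcomes contacts the therapist.
4. CAPS-5 and SCID-5-PD raters have no list access. The EMDR experience interview is done by a non-rater or takes place after the 12-month assessment.

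The cost is some reassignment of tasks within the existing team and slightly slower release of each allocation. This assumes that at least one team member is free of recruiting and rating roles; the protocol gives no staffing list to confirm that. Sample size, visits and treatment are unchanged.
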